**Methods/design:**

We will conduct a prospective, rater-masked RCT of people with ICUAW with a defined diagnosis of CIM and/or CIP in our post-acute hospital. We will randomly assign patients to one of two parallel groups in a 1:1 ratio and will use a concealed allocation. One intervention group will receive, in addition to standard ICU treatment, physiotherapy with systematically augmented levels of mobilisation (five times per week, over 2 weeks; 20 min each session; with a total of 10 additional sessions). The other intervention group will receive, in addition to standard ICU treatment, in-bed cycle sessions (same number, frequency and treatment time as the intervention group).

Standard ICU treatment includes sitting balance exercise, stretching, positioning, and sit-to-stand training, and transfer training to get out of bed, strengthening exercise (in and out of bed), and stepping and assistive standing exercises.

Primary efficacy endpoints will be walking ability (defined as a Functional Ambulation Category (FAC) level of ≥3) and the sum score of the Functional Status Score for the Intensive Care Unit (FSS-ICU) (range 0–22 points) assessed by a blinded tester immediately after 2 weeks of additional therapy.

Secondary outcomes will include assessment of sit-to-stand recovery, overall limb strength (Medical Research Council, MRC) and grip strength, the Physical Function for the Intensive Care Unit Test-Scored (PFIT-S), the EuroQol 5 Dimensions (EQ-5D) questionnaire and the Reintegration to Normal Living Index (RNL-Index) assessed by a blinded tester.

We will measure primary and secondary outcomes with blinded assessors at baseline, immediately after 2 weeks of additional therapy, and at 3 weeks and 6 months and 12 months after the end of the additional therapy intervention.

Based on our sample size calculation 108 patients will be recruited from our post-acute ICU in the next 3 to 4 years.

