### Sample size

Until now, no trials and, therefore, no specific effect size of the selected interventions for this specific population are present in the peer-reviewed literature. Our sample size calculation of 45 patients per study arm is based on a difference of 6 points in the primary endpoint of the FSS-ICU sum score between the parallel groups after 2 weeks of treatment. We assume an alpha level of 5%, a statistical power of 80% (beta = 20%) and a standard deviation (SD) of 10 using a two-sample *t* test for mean differences. Our assumption is based on the theory that the one experimental group achieves a mean of 22 points and the other group achieves a mean of 16 points in the FSS-ICU test assuming a SD of 10 in the FSS-ICU sum score and assuming that the rate of recovery of walking ability will be 0.6 in the one and 0.4 in the other group. We used the SAS (SAS Institute Inc., Cary, NC, USA) power and sample size programme for our sample size calculation. Because we consider a 20% dropout rate, a total of 108 patients (54 per study arm) would be enrolled to ensure 45 subjects in both intervention arms.

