### Recruitment

Based on our sample size calculation, 108 patients will be recruited from our post-acute ICU over the time course of 3 to 4 years. In a first cohort study in our hospital we recruited 150 patients with ICUAW and a diagnosis of CIM/CIP in approximately 18 months [26].

The research staff will follow the recruitment process of a previous study [26] and will screen lists of patients on a daily basis to recruit continuously and will monitor recruitment. Recruitment statistics for every week will be discussed to improve the recruitment and retention procedure. Based on this the research team discusses updates to recruitment and retention strategies if necessary. Based on our experience from our previous study we believe that it seems to be reasonable to recruit the anticipated sample size in our trial within 3 to 4 years.

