### Statistical methods

We will conduct both intention-to-treat and per-protocol analyses, with the intention-to-treat analysis being always the primary analysis for the primary and secondary outcomes.

Our descriptive statistics will include means and SDs, medians and interquartile ranges for continuous variables, and the number and proportions for categorical variables as appropriate [39].

We will compare the two intervention groups at baseline regarding characteristics and demographics, using two-tailed Student’s *t* tests or Fisher’s exact tests, as appropriate. Variables that differ between the groups at baseline will be considered as possible confounders and adjusted for in subsequent analyses. The global alpha level will be set at 0.05 for all comparisons. To avoid multiplicity we will use a Tukey-Kramer alpha adjustment for multiple comparisons of the same outcome. Skewed data will be analysed with nonparametric test alternatives (e.g. we will use the Mann-Whitney *U* test instead of Student’s *t* tests if data are skewed).

For the primary endpoint, the FSS-ICU, we will test the hypothesis that the sum score after 2 weeks of intervention and at follow-up will be statistically different between groups. We will consider a minimum difference of 5 points of the FSS-ICU sum score (range 0–35 points) between groups as being clinically important.

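### With 20% dropout, 54 patients per arm leave about 43, not the stated 45, so FSS-ICU power is about 78.5% rather than 80%

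*Protocol article*

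**What the plan says.** The Sample size section of the protocol article arrives at 45 patients per arm. The calculation "is based on a difference of 6 points in the primary endpoint of the FSS-ICU sum score between the parallel groups" at 2 weeks, from assumed means of 22 and 16. Its other inputs are: "We assume an alpha level of 5%, a statistical power of 80% (beta = 20%) and a standard deviation (SD) of 10", with a two-sample t test. The allowance for dropout follows: "Because we consider a 20% dropout rate, a total of 108 patients (54 per study arm) would be enrolled to ensure 45 subjects" in both arms.

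The total is carried forward. The abstract gives 108, and the Recruitment section says "Based on our sample size calculation, 108 patients will be recruited from our post-acute ICU". No section defines the 20% in another way or writes out the inflation formula.

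On the scale itself, the abstract (Methods/design) describes the FSS-ICU sum score as "range 0–22 points". The Statistical methods section has "FSS-ICU sum score (range 0–35 points", and the Outcome measures section also gives 0 to 35.

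**The concern.** A dropout rate is ordinarily a share of those enrolled. Read that way, three figures in one sentence (20% dropout, 54 enrolled per arm, 45 retained per arm) cannot all be true. The sentence says that the enrolment secures the evaluable number behind the 80% power, and under the plan's own dropout assumption it does not. What is at stake is whether the stated evaluable number and power can be relied on. The article later describes the trial as adequately powered (Limitations), and the total of 108 appears in the abstract and the Recruitment section as the result of this calculation.

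**Working it through.** **Inputs (Sample size section unless noted).** Difference 6 points (22 against 16); SD 10; alpha 5%; power 80%; two-sample t test; 1:1 allocation (Study design); dropout 20%; 54 enrolled per arm. The section does not say whether the test is two-sided. Two-sided is assumed here because it reproduces the stated 45; a one-sided test would need only 35 per arm (normal approximation).

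**Step 1: reproduce the 45.** Standardised difference d = 6/10 = 0.6. The two-sided t test at alpha 0.05 and power 0.80 (noncentral t) needs 44.59 per arm, rounded up to 45. Power at 45 per arm is 80.4%. The plan's evaluable number is confirmed.

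**Step 2: the dropout allowance.** If a share p of those enrolled is lost, enrolment N leaves N × (1 − p), so N = n/(1 − p).

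| Quantity | Calculation | Result |
|---|---|---|
| Enrolment needed to keep 45 | 45/0.8 = 56.25 | 57 per arm, 114 in total |
| Route that gives the stated figure | 45 × 1.2 | 54 per arm, 108 in total |
| Patients left from 54 at 20% loss | 54 × 0.8 | 43.2 per arm |
| Largest dropout at which 54 keeps 45 | 1 − 45/54 | 16.7% |

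Rounding on the total instead gives 90/0.8 = 112.5, so 113. The route 45 × 1.2 is inferred from the match. The inconsistency does not depend on it.

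**Step 3: power for the FSS-ICU at the numbers that remain** (d = 0.6, two-sided alpha 0.05, t test, dropouts contributing no 2-week value).

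| Evaluable per arm | Power |
|---|---|
| 45 | 80.4% |
| 43.2 (unrounded) | 78.7% |
| 43 | 78.5% |

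The normal approximation gives 79.4% at 43 per arm. The loss by t test is 80.4 − 78.5 = 1.9 percentage points.

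**Step 4: how firmly 45 is secured.** As an illustration, suppose each patient drops out independently with probability 20%. The chance that at least 45 of 54 remain is then about 34% for one arm and about 0.34² = 12% for both. Under the stated assumption the target would usually be missed, though narrowly.

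**Step 5: the scale range.** The calculation uses the means, SD, alpha and power; the range is not an input. The planning figures fit a 0–35 scale. On 0–22, a mean of 22 would be the ceiling and leave no spread, and a mean of 16 would cap the SD at √(16 × 6) = 9.8, below the assumed 10. The 0–22 in the abstract is therefore the figure out of line.

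**The case against.** The strongest reply is that the consequence is slight. The Sample size section itself says that no specific effect size exists for these interventions in this population, so 6 points and SD 10 are working assumptions. At 43 per arm an SD of 9.8 would give 80.1% power; at 45 per arm an SD of 10.5 would give 76.5%. Half a point of SD moves power by 80.4 − 76.5 = 3.9 points, about twice the loss at issue. This stands, and it limits the weight of the point. It does not make the sentence consistent.

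A second reply is that 43 is a complete-case figure. Intention-to-treat is the primary analysis, and the article does not say how dropouts' outcomes will be handled. Some of those who leave may still have a 2-week value. This also stands as a condition on the 78.5%. But the article itself treats 45 as the number left after dropout, so the comparison of 43 with 45 is on its own terms.

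A reader might go further in three ways that the document does not support:

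- **That the trial is seriously underpowered and must enrol more.** A loss of about 2 points does not show that.
- **That the abstract's 0–22 range undermines the sample size.** It does not, because the range is not used there and both Methods statements give 0–35.
- **That a baseline-adjusted analysis would certainly restore the power.** Baseline FSS-ICU is collected (Table 2), but the gain depends on its correlation with the 2-week score, which the article does not give. Dividing d by √(1 − r²) at 43 per arm gives approximately 78.9% for an assumed r = 0.1, 80.1% for 0.2, 82.2% for 0.3 and 88.8% for 0.5. Recovery needs r of about 0.2 or more.

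**Conclusion.** The point holds as an arithmetic error in a stated planning figure. With 54 enrolled per arm and 20% dropout, about 43 per arm remain. Holding 45 would need 57 per arm, which is 3 more per arm and 6 more in total than planned. The shortfall is about 2 evaluable patients per arm, and FSS-ICU power is 78.5% instead of 80.4%.

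This rests on the plan's own 6 points and SD 10, a two-sided test at 5%, and no 2-week value from dropouts. It concerns the FSS-ICU only and says nothing about power for walking ability, the other primary endpoint. The FSS-ICU range in the abstract is a separate minor slip with no bearing on these numbers.

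**What to change.** Keep 108 and restate the dropout sentence in one of two ways:

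- 54 per arm less 20% dropout gives 43 evaluable per arm and about 78.5% power for the FSS-ICU; or
- 45 evaluable per arm is reached only if dropout is at most 16.7%.

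Either costs one sentence and a slightly less favourable stated power, with no new patients and no change of design. If the sponsor prefers to keep both the 20% and the 45, the matching enrolment is 57 per arm (114), at the cost of 6 more patients and changes to the total in the abstract and the Recruitment section. The size of the shortfall does not demand that.

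If baseline adjustment is cited as compensation, give it as a range under stated correlations, not as an assured gain.

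As a separate correction, change the FSS-ICU range in the abstract from 0–22 to the 0–35 of the Outcome measures and Statistical methods sections. No calculation changes.

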### Recruitment

Based on our sample size calculation, 108 patients will be recruited from our post-acute ICU over the time course of 3 to 4 years. In a first cohort study in our hospital we recruited 150 patients with ICUAW and a diagnosis of CIM/CIP in approximately 18 months [26].

The research staff will follow the recruitment process of a previous study [26] and will screen lists of patients on a daily basis to recruit continuously and will monitor recruitment. Recruitment statistics for every week will be discussed to improve the recruitment and retention procedure. Based on this the research team discusses updates to recruitment and retention strategies if necessary. Based on our experience from our previous study we believe that it seems to be reasonable to recruit the anticipated sample size in our trial within 3 to 4 years.

### Statistical methods

We will conduct both intention-to-treat and per-protocol analyses, with the intention-to-treat analysis being always the primary analysis for the primary and secondary outcomes.

Our descriptive statistics will include means and SDs, medians and interquartile ranges for continuous variables, and the number and proportions for categorical variables as appropriate [39].

We will compare the two intervention groups at baseline regarding characteristics and demographics, using two-tailed Student’s *t* tests or Fisher’s exact tests, as appropriate. Variables that differ between the groups at baseline will be considered as possible confounders and adjusted for in subsequent analyses. The global alpha level will be set at 0.05 for all comparisons. To avoid multiplicity we will use a Tukey-Kramer alpha adjustment for multiple comparisons of the same outcome. Skewed data will be analysed with nonparametric test alternatives (e.g. we will use the Mann-Whitney *U* test instead of Student’s *t* tests if data are skewed).

For the primary endpoint, the FSS-ICU, we will test the hypothesis that the sum score after 2 weeks of intervention and at follow-up will be statistically different between groups. We will consider a minimum difference of 5 points of the FSS-ICU sum score (range 0–35 points) between groups as being clinically important.

For the primary endpoint, walking ability, we will analyse the time to regain walking ability (defined as FAC score ≥3) in a time-to-event analysis. We will calculate the probability of regaining walking ability with the Kaplan-Meier (KM, ‘survival analysis’) method [40] and will provide KM plots as appropriate with 95% confidence intervals (CI) including the number of participants at risk at each time. We will report median times until regaining walking ability with 95% CI. The assumptions of KM analysis will be tested with the implemented function of SAS/STAT 9.3 (SAS Institute Inc., Cary, NC, USA). Cox regression analysis will be used to estimate relative hazard rates of the intervention groups [41]. Time to event will be defined as the time difference between study entry (T0) and the date of reaching a FAC score equal to 3, or the possible censoring dates of discharge or treatment refusal or death, respectively. Data will, therefore, be censored appropriately if patients are discharged, refused treatment or died. We will use the log-rank test to test statistically for differences between the KM curves of the intervention groups [42]. We will use a stepwise multivariable Cox regression analysis with a variable selection to also take into account the influence of all dependent variables (PROC PHREG; best subset analysis; SAS 9.3, SAS Institute Inc., Cary, NC, USA) [41, 43]. The following dependent-variable categories will be analysed for their association with walking ability:Demographic variables at baseline (such as age and sex)All clinical variables at baseline (such as muscle strength, PFIT-S; Table 2) andMedical characteristics at baseline (such as diagnosis and duration of primary illness)

All dependent (explanatory) variables will be first described in a univariate analysis and then selected for a multivariable model based on statistical significance [44–46]. In this process an explanatory variable has to be significant at the 0.2 level to be *entered* into the multivariate model [43]. To *remain* in the multivariate model an explanatory variable has to be significant at the 0.1 level [43]. We will first select explanatory variables from a list of all univariate analysis with the highest global chi-square score into our multivariable model [43]. We will use a graphical inspection and also evaluate whether the proportional hazard assumption for an explanatory variable is met [41]. We will, for the final model selection, compare the multivariate models (with remaining variables) on the global score chi-square statistic (best subset selection) and on the Akaike’s information criterion (AIC) performed [43]. The aim of our analysis is to *explain* the dependent variable (e.g. regaining walking function) by a multivariate Cox proportional hazard model with not too many variables (to prevent overfitting) [43]. The multivariate effects of explanatory variables in the final model will be expressed as hazard ratios (HR) with 95% CI [43]. We will use SAS/STAT 9.3 for all statistical procedures (SAS Institute Inc., Cary, NC, USA).

We will do an interim analysis for efficacy and ineffectiveness after half the patients have completed our study trial. The trial will be stopped if there is a statistically significant difference between the groups in one direction at an alpha level of 0.05 at this time point of recruitment.

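### Adjustment of the FSS-ICU comparison is triggered by baseline differences between arms, so baseline FSS-ICU would usually be left out and the precision it offers lost

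*Protocol article*

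**What the plan says.** All references are to the protocol article.

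- **Adjustment rule (Statistical methods).** Baseline characteristics are compared between arms with two-tailed t tests or Fisher's exact tests. The next sentence reads "Variables that differ between the groups at baseline will be considered as possible confounders and adjusted for in subsequent analyses". No other route to covariate adjustment of FSS-ICU is stated, and the cut-off for a difference is not written.
- **FSS-ICU analysis (Statistical methods).** The hypothesis concerns the sum score after 2 weeks and at follow-up. The paragraph names neither a test nor a baseline covariate. A general sentence adds "Skewed data will be analysed with nonparametric test alternatives", with Mann-Whitney in place of the t test as the example. A difference of 5 points is called clinically important.
- **Sizing (Sample size).** The section describes 45 per arm as "based on a difference of 6 points in the primary endpoint of the FSS-ICU sum score between the parallel groups after 2 weeks of treatment". The remaining inputs, for a t test comparing two means, read: "We assume an alpha level of 5%, a statistical power of 80% (beta = 20%) and a standard deviation (SD) of 10 using a two-sample".
- **Data collected.** Table 2 schedules FSS-ICU at T0.
- **Walking (Statistical methods).** The arms are compared by Kaplan-Meier curves with a log-rank test, and a Cox regression estimates the relative hazard between groups. Separately, "We will use a stepwise multivariable Cox regression analysis with a variable selection" is planned over baseline demographic, clinical and medical variables: "In this process an explanatory variable has to be significant at the 0.2 level to be" entered and at the 0.1 level to stay, with the final choice by score chi-square and AIC. The stated purpose is to explain recovery of walking.

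**The concern.** In a randomised trial a baseline difference between arms is a product of chance. Its p-value does not measure how strongly the variable predicts outcome, and prognostic strength is what decides whether adjustment helps. A rule driven by that p-value omits a strong predictor whenever it happens to be balanced, and admits an irrelevant variable whenever it happens not to be.

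The variable most likely to matter for FSS-ICU at 2 weeks is FSS-ICU at T0, which the trial already measures. Leaving it out gives away precision that costs nothing to obtain. The rule also means that the model behind any adjusted FSS-ICU estimate is unknown until the allocated data have been examined.

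A smaller point is that a switch to Mann-Whitney on finding skewness yields a test with no estimated mean difference, and therefore no interval to set against the protocol's 5-point threshold.

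**Working it through.** **Inputs from the protocol.** Difference 6 points, SD 10, alpha 5%, power 80%, two-sample t test, 45 per arm (Sample size); important difference 5 points (Statistical methods); FSS-ICU measured at T0 (Table 2).

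**Assumptions.** The correlation rho between baseline and 2-week FSS-ICU is not in the documents; 0.3, 0.5 and 0.7 are used. A baseline difference is read as p<0.05. Alpha is taken as two-sided.

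**Step 1: reproduce the plan's figure.** The standardised difference is 6/10 = 0.6. The noncentral t calculation gives 44.6, so 45 per arm, with power 0.804 at 45. This matches "Our sample size calculation of 45 patients per study arm". A one-sided calculation gives 35 and does not match.

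**Step 2: prespecified ANCOVA.** Adjusting for baseline reduces the residual SD to 10 × √(1 − rho²): 9.54, 8.66 and 7.14 for rho 0.3, 0.5 and 0.7. The standardised differences for 6 points become 0.629, 0.693 and 0.840. The same power function gives:

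| Analysis | Power, 6 points, 45 per arm | Power, 5 points, 45 per arm | N per arm for 80% at 6 points |
|---|---|---|---|
| Unadjusted | 0.80 | 0.65 | 45 |
| ANCOVA, rho 0.3 | 0.84 | 0.69 | 41 |
| ANCOVA, rho 0.5 | 0.90 | 0.77 | 34 |
| ANCOVA, rho 0.7 | 0.98 | 0.91 | 24 |

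**Step 3: the rule as written.** With 45 per arm and 40,000 simulated trials per setting, the analysis adjusts for baseline FSS-ICU only if its own baseline t test has p<0.05, and otherwise uses the unadjusted t test. Adjustment is triggered in about 5% of trials.

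| rho | Power, stated rule | Power, ANCOVA (simulated) | Type I error, stated rule | Type I error, ANCOVA |
|---|---|---|---|---|
| 0.3 | 0.81 | 0.83 | 0.048 | 0.050 |
| 0.5 | 0.81 | 0.90 | 0.042 | 0.049 |
| 0.7 | 0.82 | 0.97 | 0.038 | 0.049 |

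The rule recovers very little of the available gain. Its type I error is at or below the nominal level; independent simulations put it at about 0.036 to 0.049 over this range of rho. The simulated ANCOVA power agrees with Step 2 to within one percentage point.

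**Step 4: irrelevant variables entering.** The number of baseline variables tested is not stated. If k independent variables are each tested at 0.05, the chance that at least one differs is 1 − 0.95^k: 26% for k = 6, 40% for k = 10, 64% for k = 20. Table 2 marks six outcome measures at T0. They overlap, so independence is only a rough guide.

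**Step 5: walking.** No power loss was calculated here, because the log-rank test and the group Cox estimate do not depend on the stepwise selection. Within the stepwise model, 10 to 20 candidates unrelated to outcome (an assumed count) would yield on average 0.2 × 10 = 2 to 0.2 × 20 = 4 that pass the entry screen by chance.

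**The case against.** **The plan meets its own target without ANCOVA.** This is true: 45 per arm gives 80% for 6 points under its assumptions. The point is therefore an improvement that costs nothing, not a failure of the sample size. It matters more at the 5-point difference that the protocol calls important, where unadjusted power is 65%.

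**The FSS-ICU test is not named, and an article may leave the model to the analysis plan.** This stands in part. The t test is known from the sizing and from the example about skewed data, not from the FSS-ICU paragraph, and the absence of a named covariate would not be a finding by itself. The adjustment rule, however, is stated outright, and that rule is what is criticised.

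**The size rests on an unstated correlation.** This stands. At rho 0.3 the gain over no adjustment is only about 3 to 4 percentage points.

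**Mann-Whitney does not hide the mean difference.** This is largely fair, since means and SDs will be described. What is missing is an interval for that difference if the data are skewed.

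**A reader might infer that the walking treatment effect comes out of stepwise selection, or that this selection wastes power.** The text does not support either reading. It specifies a log-rank test and a Cox estimate for the intervention groups, and introduces the stepwise model separately, over baseline variables and for an explanatory purpose. What remains is narrow: the text does not say whether treatment is kept in that model, and the 95% intervals of its final hazard ratios would take no account of the selection.

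**Conclusion.** The point holds for FSS-ICU. The stated rule would leave baseline FSS-ICU out of the comparison in about 95% of trials, giving power of about 81 to 82% at 45 per arm and 6 points. Prespecified ANCOVA would give about 84%, 90% or 98% at rho 0.3, 0.5 or 0.7. These figures rest on the protocol's SD of 10, normal scores, an assumed rho, and p<0.05 as the reading of a baseline difference.

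A reader might infer that choosing covariates after seeing the data raises the false-positive rate. For the rule simulated here it does not: type I error is about 0.036 to 0.049, slightly conservative. The harm is lost precision and an adjustment model settled by chance imbalance.

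The figures use 45 per arm, the number the plan intends to analyse. Its enrolment figure, "Because we consider a 20% dropout rate, a total of 108 patients (54 per study arm) would be enrolled", would leave 54 × 0.8 = 43.2 per arm after 20% dropout. That is a separate matter and does not change the comparison: at 43 per arm, power is 78.5% unadjusted and 82%, 89% and 97% with ANCOVA.

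For walking, only labelling and clarification are needed.

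**What to change.** 1. Make ANCOVA of T1 FSS-ICU on treatment and baseline FSS-ICU the primary FSS-ICU analysis. If residuals are skewed, report a robust or bootstrap interval for the adjusted mean difference, and keep Mann-Whitney as a sensitivity analysis.
2. Delete baseline significance testing as the trigger for adjustment. Baseline characteristics can still be described by arm.
3. Keep the log-rank test and the group Cox estimate as the treatment comparison for walking. Label the stepwise and best-subset Cox model as exploratory prognostic work.
4. Base any adjusted treatment hazard ratio on a model with treatment forced in and a short covariate list named in advance, for example baseline FSS-ICU, MRC sum score and age.

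The cost is wording only. FSS-ICU and MRC are already scheduled at T0 and age is already a listed candidate variable, so no patients, visits or measurements are added. The change should be made before allocated outcome data are examined.

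### The primary FSS-ICU test may change from a t test to Mann-Whitney according to the observed data, so the p value may not match the mean difference in points on which the trial is sized

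*Protocol article*

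**What the plan says.** The Sample size section of the protocol article bases 45 patients per arm on "a difference of 6 points in the primary endpoint of the FSS-ICU sum score" after 2 weeks, using a two-sample t "test for mean differences". It assumes that "the one experimental group achieves a mean of 22 points and the other group achieves a mean of 16 points", with an SD of 10.

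The general part of the Statistical methods section then states: "Skewed data will be analysed with nonparametric test alternatives". Its example is Mann-Whitney U in place of Student's t "tests if data are skewed". No endpoint is exempted.

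The FSS-ICU paragraph follows directly. It names no test. It says only that the hypothesis is that "the sum score after 2 weeks of intervention and at follow-up will be statistically different between groups", and it sets the yardstick for importance: "We will consider a minimum difference of 5 points of the FSS-ICU sum score" between groups, on a 0-35 scale.

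**The concern.** The only test that the article ties to the FSS-ICU is the t test of the Sample size section, which is the test that the skewness rule replaces. So the rule reaches the primary endpoint unless something excludes it, and nothing does. The trigger is a property of the observed outcome data.

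The two tests answer different questions. The t test asks whether the arm means differ, and it comes with an estimate and interval in points. Mann-Whitney asks whether scores in one arm tend to rank above those in the other, and it yields no difference in means. The planned effect of 6 points is a difference in means, and the 5-point yardstick is in points. If the switch is made, the p value that declares the primary result and the figure that is compared with 5 points come from different methods and need not agree.

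The fallback also fits poorly with its surroundings. The same section promises adjustment for variables that differ at baseline, and a Tukey-Kramer correction. A plain Mann-Whitney test takes no covariates, and Tukey-Kramer is a procedure for means.

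**Working it through.** **1. Reproduce the design figure.** Inputs from the Sample size section: difference 22 − 16 = 6, SD 10, alpha 0.05 (two-sided assumed), power 0.80.

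- Normal approximation: n = 2 × (1.960 + 0.842)² × 10² / 6² = 2 × 7.85 × 100 / 36 = 43.6, so 44 per arm.
- Noncentral t: n = 44.6, so 45 per arm, with power 0.804 at 45.
- A one-sided test would need only 36 per arm, so the stated 45 is two-sided.

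The stated 45 per arm reproduces, as a t test on means.

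**2. Simulate both tests under the plan's figures.** The article gives no distribution, so the shape is an assumption: score = round(35 × Beta(μk, (1 − μ)k)), with μ = mean/35 and k = μ(1 − μ)/(SD/35)² − 1.

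- Mean 22: μ = 0.629 and k = 0.2335/0.0816 − 1 = 1.86, giving skewness −0.47.
- Mean 16: μ = 0.457 and k = 0.2482/0.0816 − 1 = 2.04, giving skewness +0.15.

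Results from 20,000 trials per row, 45 per arm, SD 10 in both arms. The rule is triggered here by a skewness test at p < 0.05 in either arm:

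| Means | t rejects | Mann-Whitney rejects | Switching rule rejects | Tests disagree |
|---|---|---|---|---|
| 16 v 16 | 5.2% | 5.1% | 5.3% | 0.9% |
| 22 v 22 | 4.9% | 4.8% | 4.9% | 1.6% |
| 22 v 16 | 79.9% | 80.2% | 80.0% | 2.3% |

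Two other assumed shapes (normal and gamma, clipped to 0-35) gave the same picture. Clipping reduces the 6-point difference to 5.5 and 5.6 points and the SDs to between 8.3 and 9.3. Power was 79% (t) and 78% (Mann-Whitney) for the normal shape, and 86% and 88% for the gamma. The tests disagreed in 3.4% of trials for each. Over all shapes, the type I error of a switching rule was 4.6% to 5.4%. Even taking the smaller of the two p values gave only 5.6% to 6.2%.

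**3. How often the switch would be made.** At 22 v 16 with the beta shape, a skewness test triggers it in about 18% of trials, and a cut-off of absolute skewness above 0.5 in about 45%. Across the shapes and means tried, the skewness-test rate runs from about 1% to 59%. The documents therefore do not determine which primary test will be run.

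**4. Equal means, unequal spread.** The plan assumes one SD of 10, so these cases lie outside it. Beta shape, 45 per arm:

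| Common mean | SDs | t rejects | Mann-Whitney rejects |
|---|---|---|---|
| 22 | 10 v 8 | about 5% | about 6% |
| 22 | 10 v 6 | about 5% | about 10% |
| 24 | 10 v 5 | about 5% | about 20% |

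The switching rule follows Mann-Whitney: about 6%, 10-11% and 20-22%. Medians differ in these cases (24 v 22 for SD 10 v 6; 27 v 24 for SD 10 v 5), so Mann-Whitney is responding to a real difference in distribution, though not to a difference in means.

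**The case against.** **The reach is inferred.** The skewness sentence is general, and the t tests named just before it are for baseline comparisons. That is correct. The inference is direct, however: the FSS-ICU paragraph names no test, the design rests on a t test, and the rule has no exception.

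**The cut-off for skewness belongs in the analysis plan.** This stands. Its absence from an article is no finding. The point is the stated rule itself: however skewness is defined, the choice between two questions would still be made on the outcome data.

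**The 5-point yardstick is tied neither to means nor to a test, and arm means can be reported anyway.** This stands in part. The article promises means and medians as appropriate, so a points difference could be set beside 5 points whichever test is used. A reader might infer that the 5- and 6-point figures become unusable after a switch. That goes too far. The harm is that the p value would no longer belong to the points estimate.

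**The statistician is masked.** The Randomisation section withholds allocation from the analysing statistician. This limits steering towards a favoured arm, but it does not make the choice of test independent of the data.

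**The larger figures do not come from the plan.** This stands. A Shapiro-Wilk trigger would cause a switch in about 98% of beta-shaped trials at 22 v 16, but that is a test of normality, not a skewness criterion. The 10% and 20% rejection rates need SDs of 10 against 6 or 5, and the plan assumes a common SD of 10.

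**Conclusion.** The point holds as one of pre-specification and interpretability. The Statistical methods section lets the observed data decide whether the primary FSS-ICU result rests on a comparison of means or of ranks, although the trial is sized on means and read in points. This conclusion follows from the text and does not depend on the simulations.

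A reader might infer that the rule materially inflates the type I error, costs power or makes the sample size wrong. The documents do not support that. Under the plan's own means and SD, with the shape assumed, type I error stays near 5%, power is about 80% with either test, and the two disagree in about 2-3% of trials. The 45 per arm reproduces. Mann-Whitney rejects clearly more than 5% under equal means only if the spreads differ clearly.

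The same figures show that the switch buys nothing. With about 45 per arm on a bounded scale, the t test held its level in every equal-variance shape tried, so the fallback gives no protection in exchange for the ambiguity. The change should be made, but the point does not threaten the trial's validity.

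**What to change.** In the FSS-ICU paragraph of the Statistical methods section, name the primary analysis at 2 weeks as a difference in means, in points, with a 95% CI, whatever the distribution. Use unequal-variance or robust standard errors, or a bootstrap interval. State that the skewness rule does not apply to this endpoint, and keep Mann-Whitney as a named sensitivity analysis that does not change the primary conclusion.

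The cost is about one sentence, with no new data and no more patients. The 45-per-arm calculation then matches the analysis for which it was made, and the estimate can be read directly against 5 points.
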